### Design

A randomised clinical trial will be carried out in four health regions of the Basque Health Service (Araba, Gipuzkoa, Ezkerraldea-Enkarterri and the Bidasoa Integrated Health Organisation) involving a total of 556 DM2 patients between 18 and 79 years old, recruited proactively, as described in the section on the recruitment process below. Patients will be randomly assigned to intervention and control groups, and will be followed up over two years. Measurements will be taken at four time points: baseline, and 6, 12 and 24 months after the intervention. The research protocol has been approved by the Basque Country Clinical Research Ethics Committee (Ref. no.: 11/2010).

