### Sample size

Based on the results of a pilot study with 171 patients, we found a standard deviation (SD) of 1.2% in HbA1c and, given that that the mean SD in literature is around 2%, we used an SD of 1.5% to calculate the sample size. Considering an intra-class correlation of 0.05 [18] and an average of 10 participants per group, we calculated that we needed 277 participants per study arm to detect a clinically relevant difference of 0.5% in HbA1c levels at 12 months, with 80% power, with p-value of 0.05 and assuming a dropout rate of 15%.

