### Data analysis

The categorical variables will be presented as frequencies and percentages (%) while the continuous variables will be reported as means and SDs. Patients in the intervention and control groups will be compared on an intention-to-treat basis. To assess the intervention effect, we will compare changes observed in each of the groups using Chi-square tests for categorical variables, and Student’s t-tests for continuous variables in the two independent groups, for each of the repeated measurements. To adjust variables that may confound or moderate the effect of the intervention, we will perform stratified analysis and multivariate regression analysis. Multilevel analysis, i.e., generalized mixed-effects models, will be used to estimate baseline and multivariate-adjusted between-group mean differences, adjusted odds ratios (AORs), and 95% confidence intervals (CIs) at the patient level, taking into account the clustered structure of data for patients for whom the intervention has been led by different individuals.

Longitudinal generalized mixed models will be used to analyse the overall trend in changes in the outcome measures taking into account the repeated measurements for each patient and also the clustered structure of data. These models will be linear for continuous variables, and logistic for categorical variables. Time will be considered in these models as a continuous variable, based on linear, quadratic or logarithmic functions, or as a categorical variable, with several correlated measurements for each individual. The least restrictive option with the best fit to the data will be chosen. The intervention, the time of measurement and intervention-time interaction will be included as fixed effects in the models. Patients and leaders will be included as random effects on the intercept and on the time slope. These models will be extended to include variables that may confound or modify the effect of the intervention, this being guided by the stratified analysis. At this stage, results will be presented as coefficients with their respective 95% confidence intervals. The analysis will be performed using SAS v. 9.2, SPSS v. 19 and R.

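### The form of time in the longitudinal model is chosen by fit to the trial data under an ambiguous rule; it should be fixed in advance as categorical, with a 12-month contrast

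*Protocol article*

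**What the plan says.** The Data analysis section of the protocol article has two layers.

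The first compares the arms at each repeated measurement with t-tests or chi-square tests, and adds multilevel models for adjusted between-group differences that allow for clustering by leader. Neither is described as using a function of time.

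The second is a longitudinal mixed model for the overall trend. There, "Time will be considered in these models as a continuous variable, based on linear, quadratic or logarithmic functions, or as a categorical variable", and the choice is settled by this rule: "The least restrictive option with the best fit to the data will be chosen". Intervention, time and their interaction enter as fixed effects. Patients and leaders have random effects on the intercept and on the time slope. Results are given as coefficients with 95% confidence intervals.

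The Design section fixes the visits: "Measurements will be taken at four time points", namely baseline and 6, 12 and 24 months. The Sample size section powers the trial "to detect a clinically relevant difference of 0.5% in HbA1c levels at 12 months". The article does not say which of the planned analyses is primary.

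**The concern.** In the longitudinal model the effect of the programme over time is carried by the interaction of arm with the time function. If the trial data pick the function, they also pick what that coefficient means: a slope per month, a slope per log-month, a curve, or a set of visit differences. An interval computed as if the form had been fixed takes no account of that choice.

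This is a rule that the protocol states, not a detail left open for an analysis plan, and as worded it does not lead to one model. A smooth form also need not estimate the 12-month difference on which the trial is powered. A six-week course may well act early and then hold or fade, and a straight line cannot follow that shape.

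**Working it through.** **1. Does the rule pick one model?** There are four visits, so each arm has four means. Mean parameters per arm: linear 2, logarithmic 2, quadratic 3, categorical 4. Categorical time reproduces any set of four means, so it contains the other three forms and always has the highest likelihood.

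- Least restrictive, or best fit by likelihood alone: always categorical.
- Best fit by a penalised criterion: possibly a smooth form. Over two arms, moving from linear to categorical adds 2 × (4 − 2) = 4 parameters, which costs 2 × 4 = 8 units of AIC, and more under BIC.

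The two halves of the sentence can therefore point to different models.

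**2. The random time slope.** With categorical time there is no single slope. If it were read as a patient intercept plus three random visit effects, the covariance would have 4 × 5 / 2 = 10 parameters plus one residual variance, 11 in all. The covariance matrix of four measurements holds only 10.

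**3. Inputs for the error rate.** From the Sample size section: "we used an SD of 1.5% to calculate the sample size"; "Considering an intra-class correlation of 0.05"; "an average of 10 participants per group"; "with p-value of 0.05" (two-sided assumed); 277 per arm; 15% dropout. Hence 277 × 0.85 ≈ 235 completers per arm, design effect 1 + 9 × 0.05 = 1.45, and an effective 235 / 1.45 ≈ 162 per arm. The stated 277 serves only to set these sizes. It does not reproduce at 80% power (142 × 1.45 ≈ 206; 206 / 0.85 ≈ 243), which is a separate matter.

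Assumed, because the document gives no value: within-patient correlation 0.4, 0.6 or 0.8 with compound symmetry treated as known; log time as log(t + 1); AIC or BIC as the criterion; and the shape of the common trend.

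**4. Error rate with no true effect** (simulation, 200,000 replicates per scenario; nominal 5% Wald test of the interaction in the chosen model):

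| How the form is set | Error rate |
|---|---|
| AIC, interaction in the competing models, flat trend | 9.4–9.5% |
| same, linear trend | 8.6–9.1% |
| same, early-drop trends | 6.0–8.8% |
| BIC, interaction in the competing models | 5.4–7.0% |
| Chosen on the common trend, without the interaction | 4.9–5.1% |
| Categorical, fixed in advance | 4.9–5.1% |

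Taking the smallest p-value over all four forms gives about 10.5%, an upper bound. For the 12-month contrast from the selected model the rates are 5.4–8.1% (AIC) and 5.2–7.0% (BIC).

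**5. The 12-month effect under each form.** Take a sustained difference of 0, 0.5, 0.5, 0.5 at 0, 6, 12 and 24 months. For a straight line by least squares:

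- mean time = 42 / 4 = 10.5; mean difference = 1.5 / 4 = 0.375
- Sxx = 10.5² + 4.5² + 1.5² + 13.5² = 315
- Sxy = 0.5 × (−4.5 + 1.5 + 13.5) = 5.25
- slope = 5.25 / 315 = 0.01667 per month
- fitted arm difference at 12 months = 0.375 + 1.5 × 0.01667 = 0.40
- model-based change from baseline to 12 months = 12 × 0.01667 = 0.20

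The last two differ because the line also fits an arm difference of 0.20 at baseline, where the true difference is zero.

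True value 0.50 at 12 months; fitted arm difference, with model-based change from baseline in brackets:

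| Profile | Linear | Log | Quadratic | Categorical |
|---|---|---|---|---|
| 0, 0.5, 0.5, 0.5 | 0.40 (0.20) | 0.48 (0.43) | 0.58 (0.54) | 0.50 (0.50) |
| 0, 0.4, 0.5, 0.2 | 0.28 (0.06) | 0.34 (0.26) | 0.52 (0.51) | 0.50 (0.50) |
| growing linearly | 0.50 (0.50) | 0.61 (0.71) | 0.50 (0.50) | 0.50 (0.50) |

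**6. After selection by fit.** Badly fitting forms are mostly discarded. For a true 0.50 the mean 12-month change over the profiles tried is 0.48–0.51 with AIC and 0.41–0.53 with BIC.

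**The case against.** The best defence is that the rule governs only a model for the overall trend. The intervention effect is first assessed by visit-wise comparisons and multilevel mean differences, and the visit-wise comparisons give the 12-month difference without any time function. A reader might infer that the trial's main 12-month result and its p-value are inflated; the document does not support that. Nor does it name a test of the interaction as decisive. It promises coefficients with intervals, although an interval that ignores the selection carries the same error.

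The inflation is also conditional. The wording permits choosing the form on the pooled trend, or taking least restrictive to mean categorical, and neither reading inflates anything.

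Finally, a reader might take 0.20 as the 12-month effect under linear time, or conclude that selection generally shrinks the effect. The 0.20 leaves out the intervention main effect, which the model includes; the fitted arm difference is 0.40. That figure also requires linear time to be kept against the data. Log and quadratic forms can overstate, and the average error after selection is modest.

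All of this stands and limits the size of the point. It does not remove it. The protocol commits to none of the harmless readings and does not name a primary analysis. The t-tests ignore the clustering that the sample size allows for, so they cannot simply be presumed to be the primary analysis.

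**Conclusion.** The point holds for the longitudinal model. Its time form is left to the trial data under a rule that does not identify one model, with no criterion and no safeguard against the interaction influencing the choice. If the interaction is in the competing models, the nominal 5% error rate becomes about 6–9.5% (AIC) or 5.4–7% (BIC); otherwise it stays at about 5%. A restrictive form can misstate a 12-month effect in either direction, while after selection by fit the mean change is about 0.41–0.53 for a true 0.50.

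These ranges rest on the assumed correlations, covariance, time profiles and fit criteria, none of which the document gives. The visit-wise t-tests and the separate multilevel differences are not shown to be affected. The harm is moderate and conditional, but the remedy costs almost nothing, so the change should be made.

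**What to change.** Replace the selection sentence in the Data analysis section with time fixed in advance as categorical, with its four visits. Use a within-patient covariance suited to four visits, for example unstructured, in place of random patient time slopes. Keep the random effect for leader or group clustering. Take the effect from this model as the between-arm contrast at 12 months, so that it matches the difference used in the sample size. Label linear, quadratic and logarithmic trend models exploratory. State which of the planned analyses is primary.

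The cost is a change of wording and a few extra parameters, negligible with about 550 patients. No visit, measurement or recruitment target changes.

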## Discussion

The objective of this clinical trial is to assess the effectiveness of the SDSMP in contrast to usual care for DM2 patients within primary care in the Basque Country. This intervention, while providing knowledge concerning the disease and its management, is different from the usual health educational models in the sense that it involves peer group education and puts considerable emphasis on reinforcing attitudes and skills that enhance proactivity, such as target setting, problem solving, positive thinking, communication techniques, dealing with feelings, and proper use of prescribed treatments. This should empower patients to more actively manage their lifestyles, changing towards healthier habits and achieving improvements in diet, physical exercise, correct use of medications, and relationships with their healthcare provider, as well as with their relatives and friends.

Existing self-care education programmes [7] are based on a range of different methods and measure different variables and, further, they have not been assessed by prospective and controlled studies in our health system. On the other hand, these types of intervention are often mentioned in debates about the changes required in health systems to face the current demographic situation. It is, therefore, necessary to provide good quality evidence to guide the selection of appropriate interventions by undertaking controlled randomised clinical trials assessing their effectiveness [19].

In our health setting, the feasibility of implementing such a programme would rely on it being integrated into the everyday practice of health professionals and on gaining support and acceptance among patients as well as leaders. If this research in our setting yields the hoped-for results, this would give us a tool for improving the care provided to patients with diabetes and other chronic diseases. The courses could be adapted to different disorders and thereby improve self-care among a wider population, leading to more self-efficacy, greater quality of life, better clinical outcomes and proper use of healthcare services, and therefore a more efficient use of resources.

### Limitations of the study

The selection criteria may limit the external validity of the intervention as otherwise eligible patients with advanced age and comorbidity will be excluded. Further, it is necessary to recognise that participation in any training activity implies a degree of willingness on the part of the patient. We consider that this predisposition should not represent a bias in the study, given that performing the randomisation after patients have shown willing to participate should ensure comparability between groups. On the other hand, working patients, in particular, may have constraints on attending group sessions due to other commitments. To limit the impact of this problem, the courses will be offered at as wide a range of times as possible. The clinical workload of the health professionals involved in the research may, however, impose restrictions on the timetable of the training sessions.
